**Methods:**

A randomized controlled trial will be conducted nationally among young Australians (aged 17-24 years) who experience anxiety symptoms and drink alcohol at hazardous or harmful levels. Participants will be individually randomized on a 1:1 basis to receive the *Inroads* intervention or assessment plus alcohol guidelines. Participants randomized to the *Inroads* intervention will receive access to 5 Web-based cognitive behavioral therapy (CBT) modules and weekly therapist support via email and/or phone. The primary outcome assessment will be 8 weeks post baseline, with follow-up assessment 6 months post baseline to determine the sustainability of the intervention effects. Primary outcomes will be the total number of standard drinks consumed in the past month (assessed by the Timeline Follow-Back procedure), severity of alcohol-related harms (assessed by the Brief Young Adult Alcohol Consequences Questionnaire), and anxiety symptoms across multiple disorders (assessed by the Generalized Anxiety Disorder-7). Secondary outcomes will include alcohol outcome expectancies; functional impairment and quality of life; and symptoms of social anxiety, anxious arousal, and depression. Results will be analyzed by intention-to-treat using multilevel mixed effects analysis for repeated measures.

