### Participants

A total of 122 participants (male and female) aged between 17 and 24 years who report anxiety symptoms and hazardous or harmful alcohol consumption will be recruited into the study in 2018. This age range captures the transition from late adolescence at 17 years into the unique developmental stage of young adulthood [43].

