### Measures

Primary and secondary outcomes of the study were assessed at baseline, 8-weeks post baseline, and 6-months post baseline using validated psychometric instruments.

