### Sample Size

Previous evaluations of brief, multisession, internet-delivered interventions for young adults have indicated an effect size at post intervention of between 0.68 and 0.99 for reduction in the number of drinks consumed [39,75], 0.56 for reduction in alcohol-related consequences [75], and 0.59 for reduction in anxiety symptoms [76]. Optimal Design software [77] was used to calculate the required sample size, taking into account the multilevel analysis with a nested repeated measures design. Using a conservative approach with intraclass correlation coefficient of .55 estimated based on our adult comorbidity trial [37], power calculations indicated a sample size of 90 (45 each group) would be required to detect a moderate effect size of 0.50 between the intervention and control group with power=0.8 and alpha=.05. To allow for data attrition at post assessment, estimated at 35% (n=32/90) [78], a total sample of 122 individuals will be recruited to the study.

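### The attrition allowance adds 35% of 90 instead of dividing by 0.65: 122 recruits leave about 79 completers, not the 90 needed for 80% power

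*Protocol article*

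**What the plan says.** The Sample Size section of the protocol article works in two steps.

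- **Required number.** "power calculations indicated a sample size of 90 (45 each group) would be required". This is for 80% power at an alpha of .05, with a standardised group difference of 0.50. The calculation was done in the Optimal Design software for a nested repeated-measures design, with an "intraclass correlation coefficient of .55 estimated based on our adult comorbidity trial".
- **Allowance for loss.** "To allow for data attrition at post assessment, estimated at 35% (n=32/90) [78], a total sample of 122 individuals will be recruited".

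The Participants section repeats the target: "A total of 122 participants (male and female) aged between 17 and 24 years". Study Setting and Design makes the 8-week assessment the primary end point, and the 35% is an estimate of loss at that assessment.

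**The concern.** The second step takes the percentage of the wrong base. A 35% attrition rate describes the people who enter the trial, so it has to be applied to the number recruited. The plan applies it to the number needed at the end: the numerator 32 over the denominator 90 is 35% of the required sample, and 90 + 32 = 122. This always gives too small a target, and the error grows with the rate; at 35% it is substantial.

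What is at stake is the power claim. The section says that the recruited sample, after the expected losses, has 80% power for an effect of 0.50. If it does not, a null result would be read against a power that the design never had.

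**Working it through.** **Inputs**

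| Input | Value | Source |
|---|---|---|
| Required with data | 90 (45 per group) | Sample Size |
| Effect size | 0.50 | Sample Size |
| Power and alpha | "with power=0.8 and alpha=.05" | Sample Size; two-sided assumed, as sidedness is not stated |
| Intraclass correlation (ICC) | 0.55 | Sample Size |
| Measurements | 3: "assessed at baseline, 8-weeks post baseline, and 6-months post baseline" | Measures; that 3 was entered in the software is an assumption |
| Allocation | 1:1 | Abstract, Methods |
| Attrition | 35%, taken as 32 of 90 | Sample Size |
| Recruitment target | 122 | Sample Size; Participants |

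**Step 1. Reproduce the 90.** With m = 3 measurements and ICC = 0.55 the variance factor is (1 + (m − 1) × ICC)/m = (1 + 2 × 0.55)/3 = 0.70. The noncentrality for N participants in equal arms is N × 0.50² / (4 × 0.70), tested with N − 2 degrees of freedom.

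- The smallest N with power of at least 0.80 is 90, where power is 0.801. The plan's figure is reproduced.
- A baseline-adjusted variance factor, 1 − 0.55² = 0.6975, also gives 90 (power 0.802).
- Other two-sided forms do not. Ignoring the ICC gives 126, averaging two measurements gives 98 to 100, and a change score gives 114 to 116. A one-sided change score gives 90, apparently by coincidence.

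The required number is therefore consistent with its inputs, and the fault is confined to the next step.

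**Step 2. Reproduce the 122.**

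- Additive form: 0.35 × 90 = 31.5, rounded to 32; 90 + 32 = 122. This matches the plan.
- Correct form: 90/(1 − 0.35) = 138.46, so 139, or 140 for equal arms. This does not match.

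**Step 3. What 122 delivers.**

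- Expected completers: 122 × 0.65 = 79.3, about 79.
- Shortfall: 90 − 79 = 11, and 11/90 = 12%.
- Break-even attrition: 32/122 = 26.2%.
- Check on the correct figure: 140 × 0.65 = 91.

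**Step 4. Power at an effect of 0.50.**

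| Variance factor | N = 90 | N = 79 |
|---|---|---|
| 0.70 (three measurements) | 0.801 | 0.746 |
| 0.6975 (baseline-adjusted) | 0.802 | 0.748 |

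**Step 5. Does maximum likelihood recover the loss?** Take a compound-symmetric model with correlation 0.55 at three visits and equal baseline means, and test the 8-week group difference by a normal approximation. That approximation runs about 0.01 above the figures in step 4, so the comparison is with its own value at 90.

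| Data available | Power |
|---|---|
| 90 complete | 0.811 |
| 79 complete | 0.758 |
| 79 complete + 43 with baseline only | 0.758 |
| 79 complete + 43 with baseline and 6 months | 0.777 |

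Participants with only a baseline value add nothing to the 8-week contrast. Even if all 43 (122 − 79) returned at 6 months, power would stay below both 0.811 and 0.80.

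**The case against.** The arithmetic slip itself is hard to dispute. The other side can say the following about its weight.

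- **The loss of power is modest, and 0.50 is cautious.** It is about 5 percentage points. The section cites earlier effects of 0.56, 0.59 and 0.68 to 0.99; with 79 completers, the three-measurement formula gives power of 0.84, 0.87 and 0.95 at 0.56, 0.59 and 0.68. This is correct, and it means that the trial is not badly underpowered for the effects its authors cite. But the plan claims 80% for 0.50, and that claim is what fails.
- **The power formula is inferred.** The article does not give the number of measurements entered in the software, and the three-measurement formula describes a difference averaged over visits, not the 8-week contrast alone. This stands as a caveat on the 0.75. The baseline-adjusted form, which does address a single follow-up visit, gives the same answer, and the shortfall of 11 completers depends on neither.
- **Maximum likelihood uses partial data.** It does, but step 5 shows that it does not restore 80%. The plan itself treated 90 as the number to protect, or it would have needed no allowance.
- **The 35% may be pessimistic.** The Strengths and Limitations section presents the figures from the same cited source as treatment dropout (36.4% for substance use treatment, 34.2% for internet delivery), and the retention measures aim to keep data from people who stop treatment. Actual data loss may be lower. But the Sample Size section adopts 35% as data attrition, and its power statement has to hold at that figure.

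**Conclusion.** The concern holds. Under the plan's own 35%, a target of 122 leaves about 79 participants with 8-week data, not 90; the matching target is 139, or 140 for equal arms, which is 17 or 18 more. These figures need nothing beyond the plan's own 90, 35% and 122.

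Power for an effect of 0.50 is about 0.75 instead of 0.80, so the type II error rate rises from about 20% to about 25%. That rests on two-sided alpha and on a variance factor, from three measurements or baseline adjustment, chosen because it reproduces the plan's 90. The error biases no estimate and changes no analysis, but the recruitment target and the power claim do not agree as printed, so the statement must be corrected.

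**What to change.** Rewrite the last two sentences of the Sample Size section in one of two ways.

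1. **Keep 122 and restate the power.** For example: *With 122 recruited and 35% attrition, about 79 participants will have 8-week data, giving about 75% power for an effect of 0.50; 80% power holds only if attrition is at most 26%.* The authors should confirm the 75% with the settings they used in Optimal Design, and state the number of measurements entered.
2. **Keep the 80% claim at 35% attrition and change the target.** The recruitment figure is then 140 (70 per arm), here and in the Participants section.

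The first option costs two sentences and a less favourable power figure, with no new participants. The second costs 18 more recruits (140 − 122).

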### Statistical Analysis

Primary analyses will use multilevel mixed effects analysis for repeated measures [79,80], which is a flexible analytic approach for modeling change over time that has emerged as a flexible and rigorous method for analyzing RCT results. The approach has a number of advantages over traditional approaches, including better treatment of missing data and flexible modeling of variance at the individual level, time effects, and the within-subject covariance structure [79,80]. Models will include a random intercept, and preliminary models will be estimated and model fit statistics examined to determine the most appropriate model and covariance structure. All models will use baseline measurements as the reference point to estimate participant-specific starting points and change over time. Intervention condition will be represented by a dummy-coded variable, and the condition by time interaction will be examined to assess between-group differences in treatment response over time. Treatment dose (hours of therapist contact and module completion) will be entered as an independent variable in secondary analyses to examine moderation of treatment effects. For outcomes with evidence of significant intervention effects, Cohen *d* will be calculated from model estimated marginal means and standard errors to determine the size of effect between conditions at the relevant end point. All analyses will be carried out on an intention-to-treat basis, retaining and analyzing all participants in the intervention groups they were originally allocated to. Missing data will be accounted for in all analyses using maximum likelihood estimation, and the impact of missing data on study conclusions will be examined using recommended methods [81]. Data analyses will be conducted using Stata, version 15 [82], with significance levels set at *P*<.05 (95% CI).

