### Allocation

To avoid bias, participants will be individually randomized to either the intervention or control condition via the trial website using a computer-generated randomization sequence, which is concealed from the investigators. Automatic randomization within the Web-based program removes the potential for researcher involvement. Randomization will occur directly after completion of the online baseline assessment. Following randomization, the study psychologists ([name]) and project coordinator (KP) will be informed of group allocation to deliver the intervention (phone or chat sessions and motivational emails) to participants allocated to the intervention condition, whereas the research assistant (BL) who is responsible for reminding participants to complete follow-up assessments will remain blind to allocation status.

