#### Secondary Outcomes

Module completion, time spent, rate of completion, and number and duration of therapist contacts via email, chat, and phone will be recorded to measure treatment retention and dose. Frequency of binge drinking (past month consumption of ≥5 standard drinks on 1 occasion) will be calculated from alcohol consumption data collected using the TLFB procedure [53,54]. Symptoms specific to social anxiety will be assessed using the 12-item Social Phobia Scale and Social Interaction Anxiety Scale-short forms [58]. Items are scored on a 5-point Likert-type scale from 0 “Not at all characteristic or true of me” to 4 “Extremely characteristic or true of me.” Total scores range from 0 to 48, with higher scores indicating higher levels of social anxiety. Symptoms of anxious arousal and depression will be assessed using the 21-item anxiety and depression subscales of the Depression and Anxiety Stress Scale [59]. Items are rated on a 4-point scale (0-3), summed and doubled for each subscale. Subscale scores range from 0 to 42, with higher scores indicating greater severity of emotional symptoms. Overall, functional impairment and quality of life will be assessed by the Sheehan Disability Scale [60] *.* Participants rate the extent to which their work, social life/leisure activities, and home life/family responsibilities are impaired by their symptoms on a 10-point visual analog scale. Higher numbers indicate greater impairment. The 3 items may be summed into a single dimension of global functioning impairment that ranges from 0 “unimpaired” to 30 “highly impaired.” The 28-item Drinking Motives Questionnaire-Revised [61] will be used to assess alcohol use motives across 5 subscales: social, coping-anxiety, coping-depression, enhancement, or conformity. Each item is rated on a 5-point Likert scale ranging from 1 “almost never/never” to 5 “almost always/always.” Subscales are scored as the average across the items within a scale, which allows a direct comparison across subscales. Positive alcohol expectancies will be assessed by the 17-item alcohol tension-reduction expectancies scale [62]. Each item is scored from 0 “not at all important” to 3” very important,” with total scores ranging from 0 to 51. Higher scores indicate greater expectancies regarding the tension-reducing effects of alcohol.

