#### Assessment and Alcohol Information Control

Participants in control condition will receive assessment followed by an online information pamphlet outlining the effects of alcohol and risks of overuse, the Australian National Health and Medical Research council’s recommended guidelines for alcohol consumption, and a list of links to national telephone helplines and alcohol information websites. The information pamphlet will be available for immediate download and will also be emailed to them. Past research demonstrates that answering detailed questions about drinking alters subsequent self-reported behavior, particularly among young adult samples [70-72], and thus, it is expected that the assessment procedures in combination with information provision will lead to a modest decrease in alcohol consumption in the control group. By using an alcohol-only control condition, the *Inroads* integrated intervention can be compared with current recommendations for comorbidity management, which state that alcohol use problems should be addressed before co-occurring conditions such as anxiety [73]. Participants in the control group will be informed that they will be recontacted in 8 weeks and 6 months for follow-up surveys, and after completion of the final survey, they will be offered the *Inroads* program.

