### Safety Protocol

Before consenting to the study, the information statement will provide all participants with a list of crisis and support services. At entry to the study, participants will be screened for risk of complicated alcohol withdrawal and active suicidal ideation in the past 2 weeks, and those who screen positive will be referred to appropriate support services. For participants allocated to the *Inroads* program, the project psychologists will monitor symptoms during phone, email, and/or chat contact and via review of content submitted online. The Web-based program will provide links for participants to request additional support from the project psychologists via phone or chat room. Psychologists will provide up to a maximum of 2 hours of additional phone and/or chat support where required, and in cases where a severe deterioration or safety risk is indicated, participants will be referred to appropriate services for more intensive support. Participants in both conditions will complete assessments 8 weeks and 6 months after baseline, which provides an opportunity for symptom monitoring, and all participants will be provided with a list of support services that can be accessed should they require additional help. In addition, the trial website will automatically detect any English words or phrases entered in the program modules or assessment surveys that are consistent with the vernacular of suicidal ideation [74]. If any words indicative of suicidality are detected, a notification will be sent to the project psychologists, who will manually examine the relevant content. When manual review suggests suicidal ideation, the psychologist will contact the participant to conduct a risk assessment and provide referral to appropriate support services.

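### Treatment dose is planned as a moderator, but it arises after randomisation and is zero by design in every control, so its coefficient can only be a non-randomised association within the intervention arm

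*Protocol article*

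**What the plan says.** The protocol article's Statistical Analysis section names the variable, its role in the model and its purpose: "Treatment dose (hours of therapist contact and module completion) will be entered as an independent variable in secondary analyses to examine moderation of treatment effects". The same section makes the condition-by-time interaction the main comparison and says that all analyses follow intention to treat.

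Secondary Outcomes explains how dose is obtained: module completion is logged, and the "number and duration of therapist contacts via email, chat, and phone will be recorded to measure treatment retention and dose". Allocation fixes the order of events: "Randomization will occur directly after completion of the online baseline assessment". It also says that staff learn the allocation "to deliver the intervention (phone or chat sessions and motivational emails) to participants allocated to the intervention condition".

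The control section describes something different: "Participants in control condition will receive assessment followed by an online information pamphlet outlining the effects of alcohol and risks of overuse". Controls get the programme only at the end: "after completion of the final survey, they will be offered the" programme.

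Two sections bear on how therapist time builds up. The intervention description schedules a 30-minute phone or chat session after module 1 and another after module 4, plus a feedback email after each module. The Safety Protocol adds: "Psychologists will provide up to a maximum of 2 hours of additional phone and/or chat support where required".

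**The concern.** A moderator of a randomised effect must be a characteristic that exists in both arms and is not itself produced by allocation; baseline severity is an example. Dose fails on both counts. It is a consequence of being allocated to the intervention, and it does not vary among controls.

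Once moderation is ruled out, what remains is a comparison, within the intervention arm, of participants who took more with participants who took less. They chose, or were judged, to differ. Motivated participants may finish more modules and also drink less for other reasons. Participants with greater need may use more extra support. A report that presents the resulting slope as moderation would invite a causal reading about how much content or support is needed, and this design cannot supply one.

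There is a second risk. If dose is placed in a model beside the condition variable, the condition coefficient becomes the contrast at zero dose. That is not the intention-to-treat effect, although the section promises intention to treat for all analyses.

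**Working it through.** **Plan's own figure.** The plan gives no figure for the dose analysis. The nearest is the main comparison's sample size of 90, which was used only to check the simulation's correlation setting. With effect size 0.50, two-sided alpha 0.05 (sidedness assumed) and power 0.80, n per arm = 2 × (1.960 + 0.842)² / 0.50² = 62.8. Treating the plan's intraclass correlation of 0.55 as the baseline–outcome correlation, 62.8 × (1 − 0.55²) = 43.8, so 44 per arm and 88 in total. That is within 2 of the stated 90.

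**Step 1: dose by arm.**

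| | Intervention | Control |
|---|---|---|
| Modules by 8 weeks | 0 to 5 | 0 |
| Intervention therapist contact | varies | 0 |
| Access before the final (6-month) survey | yes | no |

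A control whose survey text is flagged for suicidality may be contacted for a risk assessment. That is safety contact, not treatment dose.

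**Step 2: what can be estimated.** Moderation means a product term, condition × dose. With dose = 0 whenever condition = 0, condition × dose = dose for every participant. The columns [1, condition, dose, condition × dose] therefore have rank 3, not 4. Dose entered without a product term can be fitted, but its slope is determined by the intervention arm alone.

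**Step 3: what drives dose.** Scheduled phone or chat time is 30 + 30 minutes = 1 hour. It follows modules 1 and 4, so it tracks engagement. Extra time is up to 2 hours, given according to need. At most 2 / (1 + 2) = 67% of phone and chat time could be need-driven. This is a ceiling, and it leaves out email time, which the plan also records.

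**Step 4: how much could it matter?** The simulation used 122 participants (61 per arm), complete data, baseline–outcome correlation 0.55, a true effect of −0.5 SD for every intervention participant, no dose effect and 4,000 runs. Modules were centred on 2.5 (range 0 to 5) and hours on 1 (range 0 to 3). Each fit was a linear regression of one follow-up on baseline, condition and dose, which is simpler than the planned mixed model. The correlation between dose propensity and the outcome residual is an assumption. Its sign was also set by assumption: more modules with better prognosis, more hours with worse.

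| Assumed correlation (absolute) | False dose effect, modules | False dose effect, hours | Condition coefficient with modules in model |
|---|---|---|---|
| 0 | 4.5% | 4.8% | −0.50 |
| 0.1 | 11.6% | 12.2% | −0.37 |
| 0.2 | 31.3% | 33.3% | −0.24 |
| 0.3 | 61.7% | 65.0% | −0.11 |
| 0.4 | 85.7% | 88.6% | +0.02 |

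Without dose in the model the condition coefficient stayed at −0.50 throughout.

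**Step 5: why the condition coefficient moves.** Intention-to-treat effect ≈ condition coefficient + slope × mean dose in the intervention arm. At correlation 0.2 the slope was −0.106 per module, so −0.236 + 2.5 × (−0.106) = −0.50. The randomised effect has been split between two terms, and neither of them is the randomised effect.

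**The case against.** The strongest reply is that the plan specifies no dose-by-condition term. It says only that dose is entered as an independent variable, and a dose or dose-by-time term can be fitted. A full analysis plan may restrict it to the intervention arm. This stands against one tempting inference, that the planned model is collinear and cannot be run: the article does not commit to such a model. It does not rescue the stated purpose. Whatever form the term takes, it carries information only from the intervention arm, so it cannot show moderation of a between-arm effect.

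A reader might also infer that two-thirds of therapist hours mark deterioration, or that therapist contact will look harmful. The documents support neither. The 67% is a maximum over phone and chat only, and no expected use of extra support is given. The Safety Protocol ties the extra time to requirement and lets participants request it, but does not say that hours follow worsening scores, and it refers severe deterioration to outside services. Because scheduled sessions follow completed modules, hours also reflect engagement, which pulls the other way.

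Finally, a complier average causal effect answers a different question from dose–response and needs an exclusion restriction. That is correct, so it is an option rather than a required replacement.

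**Conclusion.** The concern holds for the secondary dose analysis as stated. Two facts carry it, both set by the design: dose is measured after randomisation, and it is zero for controls at both end points. From these it follows, without further assumption, that the analysis cannot show moderation, and that a condition coefficient adjusted for dose is not the intention-to-treat effect.

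Confounding of the dose slope is likely rather than certain, and its size and net direction are unknown. The range of about 5% to 89% false dose findings depends wholly on the assumed correlation of 0 to 0.4, and the documents give no value for it.

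A reader might go further and take this as a threat to the trial's efficacy conclusion. It is not: the primary condition-by-time analysis does not contain dose and is unaffected. The change should still be made, because following the text as written would give a wrong secondary conclusion.

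**What to change.** In Statistical Analysis, delete the stated aim of examining moderation of treatment effects by dose. Keep therapist hours and module completion out of any model used to estimate the between-arm effect. Report both as exploratory associations within the intervention arm, labelled non-causal.

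If a causal adherence question is wanted, add a complier average causal effect analysis with randomisation as the instrument. Define exposure as any module started. A higher completion threshold would count people who received active content as unexposed. State the exclusion restriction: allocation affects the outcome only through starting a module. Say why it may fail, for example because support on request is open to the intervention arm outside the modules, and because outcomes are self-reported.

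The cost is a rewrite of a secondary analysis; the plan already records the data needed. The complier average estimate will have a wider interval and rest on an untestable assumption, and the trial gives up any causal dose–response claim.

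### Cohen d is planned only for outcomes that reach significance, so the published set of standardised effects will overstate the effects on average

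*Protocol article*

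**What the plan says.** Under Statistical Analysis, the protocol article tests each outcome through the condition-by-time interaction in a mixed model, "with significance levels set at *P*<.05 (95% CI"). It then says how the standardised effect is obtained: this "will be calculated from model estimated marginal means and standard errors to determine the size of effect between conditions". The sentence opens with a condition that limits the step: "For outcomes with evidence of significant intervention effects". The section does not name the SD that serves as divisor, and it does not provide for a d where the interaction is not significant.

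The Sample Size section gives the planning figures that set the precision of these estimates. The trial is sized "to detect a moderate effect size of 0.50 between the intervention and control group with power=0.8 and alpha=.05", with an "intraclass correlation coefficient of .55 estimated based on our adult comorbidity trial". From this, "power calculations indicated a sample size of 90 (45 each group) would be required". The section continues "To allow for data attrition at post assessment, estimated at 35% (n=32/90"), and concludes that "a total sample of 122 individuals will be recruited to the study".

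**The concern.** An estimate that must pass a significance threshold before it is shown is, on average, larger than the effect it estimates. The gap widens as power falls. The plan has three primary measures, a list of secondary outcomes and two end points, so it is quite possible that some outcomes will carry a d and others will not.

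This matters because standardised effects are what later users take from a trial of this kind. The Sample Size section itself relies on published post-intervention effects of 0.56 to 0.99, and the Strengths and Limitations section names a comparison with single-disorder interventions as the next step. If this trial supplies d values only for its significant outcomes, the next trial or a meta-analysis starts from a set that leans upward. The outcomes without a d are those where a reader most needs a size and an interval on a common scale, to tell a small effect from an imprecise estimate.

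**Working it through.** **Inputs from the Sample Size section:** planned effect 0.50, power 0.8, alpha .05, intraclass correlation .55, 90 required, 35% attrition, 122 recruited. Allocation is 1:1 (Abstract).

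**Assumptions:** two-sided test (the article does not state sidedness, but it pairs P<.05 with a 95% CI), normally distributed estimates, outcome SD of 1, and correlation .55 between baseline and follow-up.

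**1. The plan's own figure.** With a baseline-adjusted contrast the variance factor is 1 − .55² = 0.6975. Then n per arm = 2 × 0.6975 × (1.960 + 0.842)² / 0.50² ≈ 43.8, rounded up to 44, or 45 with the noncentral t. This agrees with 45 per group. An unadjusted two-sample comparison would need 63 per arm, so the planned precision does rely on the repeated measures. The adjusted contrast is therefore a fair basis for what follows.

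**2. Standard error of d at 8 weeks.** Observed per arm: 122 × 0.65 / 2 = 39.65. SE = √(2 × 0.6975 / 39.65) = 0.1876.

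**3. Smallest d that can be reported.** 1.96 × 0.1876 = 0.37.

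**4. Mean reported d.** Write δ for the true effect and a = 1.96 − δ/SE. Ignoring the negligible opposite tail, E[d | significant] = δ + SE × φ(a) / Φ(−a).

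For δ = 0.50: δ/SE = 2.666, a = −0.706, φ(a) = 0.311, Φ(−a) = 0.760. The mean is 0.50 + 0.1876 × 0.311 / 0.760 = 0.577, a ratio of 1.15.

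The same formula over a range of true effects:

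| True d | Chance of being reported | Mean reported d | Ratio |
|---|---|---|---|
| 0.30 | 36% | 0.495 | 1.65 |
| 0.40 | 57% | 0.530 | 1.32 |
| 0.50 | 76% | 0.577 | 1.15 |
| 0.56 | 85% | 0.612 | 1.09 |
| 0.59 | 88% | 0.632 | 1.07 |
| 0.68 | 95% | 0.700 | 1.03 |

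The article plans on 0.50. It cites 0.56, 0.59 and 0.68 (the low end of 0.68 to 0.99) from earlier studies. The rows for 0.30 and 0.40 are my assumption and show what happens if the true effect is smaller than planned.

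**5. Sensitivity to precision.**
- With a plain change-from-baseline contrast the factor is 2 × (1 − .55) = 0.90. The threshold is then 0.42, and the mean reported d is 0.62 for a true 0.50 and 0.55 for a true 0.30.
- With no attrition (61 per arm, adjusted) the threshold is 0.30, and the means are 0.53 and 0.42.

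**6. Without the filter.** If every outcome gets a d, the average of the estimates is the true effect: 0.50 for a true 0.50.

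**The case against.** The strongest reply is that the rule changes no d that is reported. A significant outcome has the same estimate with or without it, and the tests and model estimates are untouched. That is correct. The bias lies in the set of d values on display, not in the analysis. It is also modest, 3% to 15%, if the true effects lie between the low end of the cited alcohol-consumption range (0.68) and the planned 0.50. The larger percentages need true effects below 0.50, which the article does not predict.

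Two stronger readings are tempting, and the article supports neither.

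- A reader might infer that standard errors will stand in for standard deviations and so inflate d. The text says that d is derived from marginal means and standard errors. It does not say that the standard error is the divisor. Means, standard errors and group sizes are enough to recover an SD as SE × √n, which is a usual route. In a simulation of a random-intercept model (61 per arm, correlation .55, 35% missing at each follow-up, true d 0.50), this route gave a mean d of 0.55 with the observed n and 0.44 with the randomised n. The result depends on which n is used, but there is no systematic exaggeration. That the divisor is unnamed is, on its own, a detail an article may leave to the analysis plan.
- A reader might infer that non-significant outcomes will be published with no estimate or interval at all. Only Cohen d is restricted. Nothing says that model differences or their confidence intervals will be withheld.

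**Conclusion.** The point holds as a matter of selective reporting. The article fixes a rule that makes the standardised effect conditional on P<.05. It is not a detail left open, because an analysis plan that reported d for every outcome would depart from it. With about 40 observed per arm, a baseline-adjusted contrast at correlation .55 and a two-sided .05 test, no d below about 0.37 would appear. The average reported d would be about 0.58 for a true 0.50, 15% too high. The excess grows for smaller true effects (about 0.50 reported for a true 0.30) and shrinks for larger ones. These figures concern the 8-week end point and rest on normal estimates and on attrition of 35%. Better retention would reduce the bias, and a less efficient contrast would increase it. The primary tests and their error rates are not affected.

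**What to change.** Delete the significance condition. For every primary and secondary outcome, at 8 weeks and at 6 months and whatever the P value, report:

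- the model-based between-group difference with its 95% CI;
- a standardised effect with its CI, obtained by dividing the difference and its limits by one prespecified SD.

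The pooled observed baseline SD of both arms is one reasonable divisor. It avoids back-calculating an SD from mixed-model standard errors, where the choice of n matters. It needs one caution for the GAD-7. Entry can be by a GAD-7 score of 5 or more, and Table 1 lists the pre-allocation GAD-7 at the eligibility screen, so selection on the score may narrow this SD and raise d. The report should say so, or another SD should be fixed in advance for that outcome.

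The cost is one changed sentence and a few extra table columns. No new data are needed, and neither the primary tests nor the sample size changes.
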